### Measures

#### Outcomes

Derived from the legislated aims of the MSIR, the primary outcomes will be observed reductions in all-cause and drug-related mortality and ambulance attendances for non-fatal overdose. Secondary outcomes include reductions in drug-related hospitalisations such as injecting-related injuries and infections, and increased uptake of OAT (where indicated) and other non-acute health services.

#### Exposures

The primary exposure for the SIRX Study is time-varying frequency of MSIR use. Participants will be categorised as frequent (≥weekly) or infrequent (<weekly) users of the MSIR based on facility utilisation rates determined from MSIR client database records, which will vary across time as people change their frequency of MSIR use. For the SuperMIX Cohort, participants will also be able to be categorised as frequent (≥50% of their injections) or infrequent (<50% of their injections) users of the MSIR facility on the basis of self-report questions currently implemented in the SuperMIX survey, which collects information on the proportion of injections that took place in the MSIR in the past month.^74^ Analyses using this MSIR frequency threshold have been previously published.^38^ Sensitivity analyses will be considered to explore the MSIR use thresholds. Non-MSIR controls will be SuperMIX Cohort participants who indicate they have not used the MSIR, which may change over time.

### Statistical analyses

#### SIRX-R cohort

*Mortality*. We will undertake appropriate survival modelling (eg, Cox regression or parametric (accelerated failure time or proportional hazards)) to estimate the association between MSIR use and mortality, taking account of factors that might confound the association. In these models, MSIR use will be estimated as a time-varying exposure using person-period/episode split data. Prior use of the MSIR (before SIRX Study enrolment) will be considered when accounting for possible left truncation bias in these analyses. To provide more robust causal inference using data from the SIRX-R Cohort, we will also explore application of a case-time-control method to provide fixed effects estimation implicitly controlling for all time-invariant measured and unmeasured confounders (eg, prior overdose history, time since first injection, prior level of healthcare usage and treatment utilisation, general health at baseline, sex).^75^ This statistical model will be implemented via an exposure/outcome reversed conditional logistic regression analysis on discrete-time participant-period data representing the follow-up durations for each participant (eg, days), ending in either death or censorship.

*Ambulance-attended non-fatal overdose*. We will undertake generalised linear mixed modelling (GLMM, for example, Poisson (with bootstrapped standard errors) or negative binomial) on person-period data (ie, repeated ambulance-attended overdoses per participant measured periodically) to estimate the association between MSIR use and ambulance-attended non-fatal overdose. As stated for mortality analyses, we will implicitly control for all measured and unmeasured time-invariant confounders, a fixed-effects generalised linear modelling (Poisson or negative binomial) approach will be also explored using person-period data.

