#### Record linkage data

Record linkage to routinely collected administrative data sources to measure health service utilisation will occur over the study period, with participants also requested to consent for longer-term record linkage. Using the SuperMIX Cohort record linkage framework,^16^ participants will be asked to consent for linkage to databases capturing MSIR facility use, specialist and primary healthcare consultations, prescription medication dispensations, Victorian emergency and tertiary health service presentations, specialist drug treatment service contacts, criminal justice contacts, and death records. All databases are outlined in table 2. Linkage will be undertaken by accredited linkage authorities following approval from all data custodians. Linked data are deidentified and will be stored in a secure data storage and analysis environment such as the Sax Institute’s Secure Unified Research Environment (SURE).^73^ All analysis outputs are reviewed by the Sax Institute for compliance with data custodian requirements to ensure participant privacy is maintained.

**Table 2 T2:** Administrative databases for linkage

Source database	Description	Key variables
MSIR Client Database*	Records of all client visits to the MSIR.	Visit date and time to determine number of visits per person.
MSIR Medical Record*	Records all on-site health and social services.	Medical comorbidity and on-site service provision.
Medicare Benefits Schedule (MBS)	Records of all primary healthcare services provided through government subsidised programme.	Service date, Medicare item number and description.
Pharmaceutical Benefits Scheme (PBS)	Records of all dispensations of medications available through the government-subsided programme.	Date of dispensation, medication type.
Victorian Admitted Episodes Database (VAED)	Records of all admissions and separations from Victorian hospitals.	Admission date and time, separation date and time, primary and secondary diagnoses, treatment procedures.
Victorian Emergency Minimum Dataset (VEMD)	Records of all presentations to Victorian hospital emergency departments.	Arrival date and time, separation date and time, mode of arrival, triage category, primary and secondary diagnoses, departure status.

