#### Missing data treatment and attrition

Depending on the specific analysis being undertaken, a range of missing data strategies will be considered in terms of missing data and attrition. For analyses which entail GLMM, maximum likelihood estimation will be used, and this provides unbiased effect estimates using all participant observations assuming missingness due to attrition takes a missing-at-random (MAR) process (ie, missingness can be not ‘missing-completely-at-random’ (MCAR) and can depend on model covariates and the outcomes themselves at prior occasions (incl. random intercepts)). For MSMs, use of inverse probability treatment weights will incorporate a censoring weight component (based on covariates known to predict study drop-out). SCMMs produce unbiased estimates in the face of attrition when regression models include covariates known to predict study drop-out. Where there is considerable missing data on covariates in these analyses (eg, >10%), either multiple imputation or where possible (GLMM, linear mixed modelling (LMM)) full information maximum likelihood (FIML, implemented in Mplus) will be used for unbiased (assuming MAR) missing data treatment. Finally, in all survival analyses, we will perform sensitivity analyses to estimate the extent to which right-censoring in the data (including attrition) is informative with respect to the participant’s hazard of the outcome (eg, participants with a high hazard of non-fatal overdose may be more likely to be lost to follow-up). Non-informative censoring is a key assumption of survival analysis.

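### SIRX-R mortality models set no rule that the MSIR exposure window closes before the risk period, so reduced attendance before death could pass for a protective effect

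*Protocol article*

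**What the plan says.** In the protocol article, Exposures: "Participants will be categorised as frequent (≥weekly) or infrequent (<weekly) users of the MSIR based on facility utilisation rates determined from MSIR client database records". The same section makes this classification time-varying, so a client moves between categories when attendance changes. The length of the window over which the rate is computed is not given.

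Under Statistical analyses, SIRX-R cohort, Mortality, the survival models are described thus: "MSIR use will be estimated as a time-varying exposure using person-period/episode split data". A case-time-control analysis will also be explored, as a conditional logistic regression with exposure and outcome reversed, on "discrete-time participant-period data representing the follow-up durations for each participant (eg, days), ending in either death or censorship". Its stated advantage is "fixed effects estimation implicitly controlling for all time-invariant measured and unmeasured confounders".

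Table 2 (Record linkage data) lists the content of the MSIR client database: "Visit date and time to determine number of visits per person". Exposure can therefore be dated to the day.

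Two kinds of sensitivity analysis come near the issue. Exposures mentions varying the thresholds for MSIR use. Missing data treatment and attrition says of every time-to-event model: "we will perform sensitivity analyses to estimate the extent to which right-censoring in the data (including attrition) is informative". All-cause and drug-related mortality are both primary outcomes (Outcomes).

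**The concern.** A time-varying exposure supports a causal reading only if it is measured before the event it is meant to influence. Here the exposure is attendance, and attendance can fall because a person is becoming seriously ill. All-cause mortality includes deaths preceded by illness. If the visit rate attached to the risk period includes the last days or weeks of life, some people who were weekly clients are counted as infrequent when they die. The deaths move between groups while the person-time hardly changes.

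The case-time-control model is the most sensitive. Each decedent contributes one death row, the last, and the estimate rests on comparing exposure on that row with exposure on the same person's earlier rows. Removing fixed personal characteristics does not help, because a fall in attendance before death is a change within the person. Clients who do not die supply the background time trend but have no such fall, so they do not cancel it.

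At stake is whether a protective HR for a primary outcome can be read as an effect of the facility.

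**Working it through.** **1. The plan's own figure.** Inputs: 1800 SIRX-R participants (SIRX-R cohort, recruitment); baseline mortality 1.1 per 100 person-years, 80% power, 5% significance and minimum detectable HR 0.42 (Statistical power, Table 3). Assumed here: two-sided test, 1:1 split, 3 years of follow-up, no attrition.
- Events required (Schoenfeld): 4 × (1.960 + 0.842)² / (ln 0.42)² = 41.7, so 42.
- Events expected: 900 × (1 − e^(−0.033)) + 900 × (1 − e^(−0.033 × 0.42)) = 29.2 + 12.4 = 41.6.

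The 0.42 is reproduced and is not in dispute.

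**2. Shifted deaths under no effect.** With equal person-time and no true effect, each group has D deaths. If a fraction f of frequent users' deaths is recorded as infrequent, frequent has D(1 − f) and infrequent has D(1 + f), so the apparent HR = (1 − f)/(1 + f).

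With no effect, expected deaths are 1800 × (1 − e^(−0.033)) = 58.4. The approximate chance of a significant protective result is Φ(√(58.4/4) × |ln HR| − 1.96), where √(58.4/4) = 3.82.

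| f (assumed) | Apparent null HR | Chance of significance |
|---|---|---|
| 0.1 | 0.9/1.1 = 0.82 | Φ(0.77 − 1.96) = 0.12 |
| 0.2 | 0.8/1.2 = 0.67 | Φ(1.55 − 1.96) = 0.34 |
| 0.3 | 0.7/1.3 = 0.54 | Φ(2.37 − 1.96) = 0.66 |

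**3. Illustrative simulation, no true effect.** Visits are Poisson, with personal rates drawn from a gamma distribution (shape 0.7, mean 1.2 per week; assumed). Frequent means at least one visit per week on average over the window. The apparent ratio is the odds of being frequent at death divided by the odds in other person-time.

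| Complete look-back window | Change before death (assumed) | Gap before risk day | Ratio |
|---|---|---|---|
| 28 days | none | none | 1.00 |
| 28 days | stops for 14 days | none | 0.43 |
| 28 days | halves for 30 days | none | about 0.42 |
| 90 days | stops for 14 days | none | 0.81 |
| 90 days | halves for 30 days | none | 0.80 |
| 28 days | halves for 30 days | 14 days | 0.68 |
| 28 days | halves for 30 days | 30 days | 1.00 |

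A gap removes the artefact only if it covers the decline. In a simplified paired case-time-control version with the 28-day window and no gap, the ratio was about 0.1 for either decline. It returned to about 1.0 when the gap covered the decline.

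**4. Truncation of the last period by death, with no decline.** If visits are divided by the time actually observed, the ratio is 0.78 for 28-day periods, 0.93 for 90, 0.97 for 180 and 0.99 for 360. Across other assumed visit distributions it is 0.60 to 0.86 at 28 days and 0.80 to 1.01 at 90 days. If a raw count is held against the full-period threshold, it is 0.35 to 0.39 over 28 to 360 days. Truncation therefore matters for short periods or raw counts. It is usually small for rates over 90 days or more, and absent with a complete look-back window.

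**The case against.** The strongest reply is that the article nowhere says exposure is taken from the period in which death falls. A reader might infer this from the words about periods ending in death, but they describe how follow-up ends, not when use is measured. That stands. The finding is the absence of an ordering rule, not a stated same-period exposure.

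It can be added that window and lag are details for a full analysis plan, and that case-time-control is only to be explored. This has force. However, the article does name the model, the data layout and an example period length, and it offers the case-time-control design as the route to more robust causal inference. The order of exposure and death is what that claim rests on.

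A reader might also infer that truncation alone produces a large bias. The documents do not support this. Exposure is a weekly rate, which cannot be read from a single day, so daily rows need a longer window, and a complete look-back window has no truncation bias.

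Nor do the documents show that the bias must favour the facility. They report nothing about visits before death, and escalating use would push the estimate the other way. Drug-related mortality is plausibly less open to the illness mechanism.

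The survival models will adjust for confounders, and the SuperMIX section says postulated data-generating processes will help to inform regression modelling. Either could lead the investigators to a lag, but neither sets one.

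Finally, a facility that responds to overdose on the spot may act at once, so a true effect could also weaken under lagging. That stands and limits how lagged results may be read.

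**Conclusion.** The concern holds as a conditional one. The SIRX-R mortality analyses as laid out do not prevent use close to death from counting as exposure. If use is analysed contemporaneously, reverse causation could make frequent use look protective with no true effect. Adjustment for time-invariant confounders, threshold sensitivity analyses and informative-censoring analyses do not cover this.

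The size is unknown. The null HRs of 0.82, 0.67 and 0.54 rest on assumed shifts of 10%, 20% and 30%, all in one direction, and on equal person-time. Matching the detectable HR of 0.42 would take f = 0.58/1.42 = 0.41. That is a break-even value, not evidence that so large a shift occurs. The simulated ratios depend equally on assumed visit patterns and declines. What can be said is that plausible-looking declines give artefacts large enough to matter for a primary outcome, and that the direction is not certain.

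**What to change.** For the SIRX-R mortality survival models and the case-time-control model, state that exposure in period t is computed from dated MSIR visits in a fixed look-back window that ends before t, and never from the period containing death.

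Repeat the all-cause mortality analyses with longer lags, for example 1 and 3 months, because a short gap removes the artefact only if it covers the decline. Report drug-related mortality alongside and interpret the set jointly. Attenuation under lagging signals possible reverse causation but may also reflect a real short-term effect, so it should not be an automatic reason to discard an estimate.

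The cost is wording and recoding of visit records that are already to be linked. The first weeks of follow-up supply exposure only, unless visits before enrolment are used. Recent changes in use are partly misclassified, which can dilute an acute effect.

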#### SuperMIX cohort

*Mortality and ambulance-attended non-fatal overdose*. To estimate the total causal effect (also referred to as the average causal treatment effect) of participant, MSIR use on mortality and ambulance-attended non-fatal overdose suitable causal inference statistical modelling (eg, marginal structural modelling^76^ (MSM) or sequential conditional mean modelling^77^ (SCMM)) will be undertaken on annual participant person-period data. In both these modelling methods and through different adjustment approaches (inverse probability weighting (IPW) for MSM and prior confounder/measure conditioning for SCMM possibly combined with IPWs to provide doubly robust estimation), time-independent and time-dependent confounding can be adjusted for to estimate total causal effects, without risk of introducing over-control bias (time-dependent confounding). We propose the application of MSM and/or SCMM given key differences between the methods in terms of levels of flexibility, bias and ease of implementation (ie, handling missing data and dropout, exposure and covariate interactions, estimation for continuous exposures, covariate/confounder history imbalance across exposed and unexposed treatment groups and precision; all favouring SCMM) and the ability to estimate direct longer term (*not total*) causal effects if required (only possible with MSM). Generalised linear modelling and generalised estimating equations will be used to implement MSMs and SCMMs respectively, with the appropriate distributional assumptions and link functions applied given specific outcome measurement (event-history modelling for morbidity and non-normal repeated measures estimating equations for ambulance-attended non-fatal overdose). Data-generating processes will be postulated using directed acyclic graphs, and these will inform the necessary structure of the statistical models to enable identification and estimation of total causal effects. Data-generating processes will also help inform the application of regression modelling.

#### Missing data treatment and attrition

Depending on the specific analysis being undertaken, a range of missing data strategies will be considered in terms of missing data and attrition. For analyses which entail GLMM, maximum likelihood estimation will be used, and this provides unbiased effect estimates using all participant observations assuming missingness due to attrition takes a missing-at-random (MAR) process (ie, missingness can be not ‘missing-completely-at-random’ (MCAR) and can depend on model covariates and the outcomes themselves at prior occasions (incl. random intercepts)). For MSMs, use of inverse probability treatment weights will incorporate a censoring weight component (based on covariates known to predict study drop-out). SCMMs produce unbiased estimates in the face of attrition when regression models include covariates known to predict study drop-out. Where there is considerable missing data on covariates in these analyses (eg, >10%), either multiple imputation or where possible (GLMM, linear mixed modelling (LMM)) full information maximum likelihood (FIML, implemented in Mplus) will be used for unbiased (assuming MAR) missing data treatment. Finally, in all survival analyses, we will perform sensitivity analyses to estimate the extent to which right-censoring in the data (including attrition) is informative with respect to the participant’s hazard of the outcome (eg, participants with a high hazard of non-fatal overdose may be more likely to be lost to follow-up). Non-informative censoring is a key assumption of survival analysis.

### Statistical power

Table 3 below details the approximate minimum detectable differences for mortality and non-fatal overdose analyses based on the expected distribution of participants in each cohort. Monte Carlo simulation modelling (using generalised linear mixed modelling (GLMM)) was used to estimate minimum detectable differences for non-fatal overdose and an exponential proportional hazards parametric survival model used for mortality. Baseline hazards (mortality: 1.1 per 100PY) and incidence rates (non-fatal overdose: 8.8 per 100PY) applying to each comparison were taken from current SuperMIX cohort data,^78^ as were the means and variance components used for the longitudinal GLMM simulations. All effect size estimations assumed 80% power and 5% significance. For Monte Carlo simulated analyses (n=300 replications), simulations were based on three annual outcome measurements and expected cohort attrition (SuperMIX analyses) of 30% in year 1 and 25% thereafter.

**Table 3 T3:** Minimum detectable effect sizes for outcomes

SIRX study	Comparison	Mortality (HR)	Non-fatal OD (IRR)
SIRX-R Cohort	Frequent (weekly) vs infrequent (<weekly) use	0.42	0.69
SuperMIX Cohort	Frequent (≥50% all injections) vs no use	0.3	0.58
SuperMIX Cohort	Infrequent (<50% injections) vs no use	0.37	0.64

IRRincidence rate ratioODoverdoseSIRX-RSupervised Injecting Room Registration CohortSuperMIXMelbourne Injecting Drug User Cohort

### Economic evaluation

Cost data will be available to enable economic modelling. Health economic outcomes will be considered from a government perspective, compared across the categories of MSIR exposure after weighting for cohort size. The main outcomes will be (1) the difference in total annual costs; (2) the cost per life saved; and (3) the cost per quality-adjusted life year (QALY) gained. Total costs will include costs associated with MSIR use (calculated from financial documentation and budgets over time), costs of ambulance callouts for overdoses (available on Ambulance Victoria website), healthcare costs (matching linked healthcare usage data with corresponding MBS/PBS codes, in particular costs associated with managing blood-borne virus or injecting related injuries), and OAT treatment costs. QALY gains will be estimated based on additional OAT uptake, treatment of comorbidities (eg, person-years lived with hepatitis C), changes in employment, and deaths averted that are attributable to the MSIR. Cost per QALY gained outcomes will enable benchmarking of the MSIR against other health interventions.

## Patient and public involvement

The SIRX Study was designed in partnership with key stakeholders including Harm Reduction Victoria, the representative body for people who use and inject drugs in Victoria; North Richmond Community Health, the primary health service operating the Melbourne MSIR; cohealth, a not-for-profit community health organisation providing health services including services and support for alcohol and other drugs; and the Victorian State Government. These stakeholders, along with study investigators, contribute to ongoing oversight of the study via their involvement in the SIRX Study Research Advisory group.

## Discussion

The SIRX Study has been designed to provide new evidence on the effects of SIFs in reducing overdose deaths and drug-related harms within the Australian context. Previous research has highlighted the benefits of the Melbourne MSIR but is limited by short evaluation timeframes, reliance on ecological data, or the absence of temporality to control for confounding and determine causation.^38 50 58^ Drawing on the cohort methodology used to evaluate the Insite SIF in Canada,^66^ our study aims to generate quantitative evidence of the impact of the MSIR including its model of on-site health and social service delivery, overcoming the limitations described above. The results can be used to inform decisions about the value of SIFs in general, and the specific value of a model embedding the SIF within a range of on-site health and social services.

